### Recruitment

With permission, recruitment posters are displayed on the main bulletin boards of the university by researchers, mainly the first authors. The procedure of accessing the written explanation and consent form is given to the target person who is contacted by a researcher (mainly the first author) via e-mail. Through snowball sampling, we also ask an acquaintance of the participants to introduce the recruitment poster. We aim to reach the number of targets within 1 year from the start of recruitment, but if there is a shortage, we will continue to make posters at the university and increase the number of recruitment by snowball sampling.

### Screening and informed consent

Simultaneously, as the consent procedure, a self-administered questionnaire survey of baseline data are conducted, and the explainer confirmed the drinking status and average drinking amount during questionnaire collection. The procedure for explanation and consent is mainly conducted by the first author. With written consent, the intervention group is tested for alcohol-metabolizing enzyme genotype using saliva. The explainer collect and mail the sample to the testing institution on the day of the test. On the consent form, participants will be asked if they agree to the use of their data, should they choose to withdraw from the trial. Participants will also be asked for permission by the research team to share relevant data with people from the universities participating in the study or, if necessary, from regulatory agencies. If the consent and permission are confirmed, the data can be used and shared. This study does not include collecting biological specimens for storage.

During the time of study planning and implementation, measures against coronavirus disease 2019 (COVID-19) are required. Informed consent is supposedly obtained in person; however, depending on the participant’s wishes and place of residence (during homecoming, etc.), explanation, consent, and inspection procedures are performed online and by mail, as necessary.

### Randomization

In randomization, we simply used a computer-generated random number table, collate participants with anonymizing identification numbers, and assign them to the intervention group or the control group (100 participants per group). The first author mainly marked the random number table as the identification number of the intervention group before the start of recruitment and assigned it in the order of registration depending on the presence or absence of the mark.

### Measures

From the self-written questionnaire anonymized by an identification number, basic attributes (age, sex, main areas of learning, living with or without family, work situation, participation in circles, and hobby activities) and evaluation items will be investigated. For the intervention group, we will collect data 1 month after the intervention, and 3 and 6 months after the questionnaire survey at the time of consent procedure.

At the same time as the questionnaire survey, the content and amount of drinking will be recorded in a drinking calendar for half a year anonymized by the identification number. For the questionnaire and drinking calendar, the researchers (mainly the first author) will ask the participants to answer by e-mail, and the data from the returned attached file will be collected. We will ask for a response within a week from the survey point, and if there is no response, we will optionally request a response by reminder email within a month.

### Primary outcome measures

According to participants’ average amount of daily drinking (g = pure alcohol, 1 drink = 10 g of pure alcohol), we will compare the effects of interventions by adding information on the genotypes of alcohol-metabolizing enzymes to the content of conventional teaching materials.

The questionnaire provides the following examples of the drink conversion table for alcoholic beverages (Sake: 15% alcohol concentration, 180 ml = 2 drinks; beer: 5% alcohol concentration, 500 ml [medium bottle/medium mug or can beer] = 2 drinks; whiskey brandy: 43% alcohol concentration, 60 ml [double] = 2 drinks; shochu: 25% alcohol concentration, 100 ml [cup half ] = 2 drinks; canned shochu: 7% alcohol concentration, 350 ml = 2 drinks; cocktails, fruity taste, etc.: 5% alcohol concentration, 350 ml [canned] = 1.5 drinks, 500 ml [canned] = 2 drinks; wine: 12% alcohol concentration, 150 ml (glass ) = 1.5 drinks; plum wine: 12% alcohol concentration, 90 ml [small glass] = 1 drink). We ask the answer of the average number of drinks on the drinking day of the past month.

A similar example is shown in the drinking calendar, and the drinking contents (alcohol type and alcohol concentration) and amount on the day of drinking will be recorded for half a year. From the record of the calendar, the sum of the drinking amount (pure alcohol amount) and the number of drinks is calculated using the following generally accepted formula: amount of liquor (ml) × degrees or %/100 × 0.8 (specific gravity) = pure alcohol content (g).

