**Methods:**

Participants comprised university students and staff aged 20–30 years who had consumed ≥40 g (males) or ≥20 g (females) of pure alcohol; they were classified into intervention and control groups using a simple randomization method. Participants anonymously filled out questionnaires linked to identification numbers and recorded the drinking days and amounts on the drinking calendar. The intervention group will then be tested for genotype testing using saliva (5 types of combinations of *ALDH2* and *ADH1B* enzyme activities); the result report will arrive approximately 1 month later. We will conduct a 30-min face-to-face or online intervention. The control group will be merely given the conventional materials, and genetic testing will be performed voluntarily after 6 months (end of study). The intervention group will undergo questionnaire surveys 1 month after the intervention and 3 and 6 months after baseline. Questionnaire surveys will be conducted 1, 3, and 6 months after baseline for the control group. The average amount of drinking before and after the intervention, attribute/baseline data between the two groups, and time-series data were compared using various analysis tools. For interventions, we engaged in dialog based on intervention materials that added genotyping content to the existing materials, result reports, baseline data, and drinking calendar records. Participants’ ingenuity is respected to support their drinking behavior and goal setting.

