### Statistical analysis

Baseline data and participant attributes, average drinking amount on drinking days, AUDIT-C and AUDIT scores, and response at each scale of secondary outcome measures at each measurement point will be analyzed by a descriptive statistic.

Furthermore, baseline data, attributes, and changes in the average daily drinking amount (1 drink = 10 g of pure alcohol) before and after intervention are compared with the differences between the two groups. We will also compare the measurement points within the groups and compare the groups in terms of genotypes. For these analyses, we use the *t*-test, paired *t*-test, Wilcoxon rank-sum, chi-square, Mann–Whitney *U*, and Kruskal–Wallis tests as appropriate. The selection of the analysis method depends on the parametric and nonparametric data obtained from the results of descriptive statistics and normality tests to determine. In addition, the change in the average amount of drinking (1 drink = pure alcohol 10 g) in each group is examined by calculating the effect size. Data will be analyzed using IBM SPSS Statistics for Windows version 28. If the intervention is not possible in the intervention group, or if no response will be obtained after 1 month in the control group, it will be excluded from the analysis.

Regarding qualitative data (positive aspects about the alcohol constitution test, reasons, etc.), we will examine them by using an inductive analysis method with qualitative coding. The code extracted to ensure reliability will be analyzed by multiple researchers, including those with qualitative research experience.

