### Conventional teaching materials

In the control group, the conventional teaching materials (alcohol handbook for university students) [33] will be handed over to the participants during the consent procedure and requested to be read. The survey will only be conducted for half a year by providing the conventional materials.

The main contents of the conventional materials are also included in the abovementioned test result report and health guidance materials for intervention. Although some descriptions are duplicated, the main contents are as follows:A recall of experiences such as the loss of a child or parent resulting from a fatal accident or illness caused by drinking alcohol, or a dangerous experienceCurrent drinking style of university students (results of the drinking attitude survey)Conversion of the amount of alcohol consumed on the day of drinking according to a conversion table and checking of the current amount of alcohol consumed by using the alcohol consumption ranking table (male, female)Stage from tipsy to death resulting from acute alcohol intoxicationBinge drinkingChecking, defining, and coping with alcohol and harassmentSpecific examples of ideas for keeping tipsy at drinking partiesKnowledge of alcohol (alcohol-related problems: violence, depression, sleep-related problems, family and workplace problems, mental and physical illnesses caused by alcohol, etc.)

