As mentioned in the introduction, a randomized controlled trial using the genetic information of the alcohol-metabolizing enzyme *ALDH2* validated the effect 30 days after providing Internet-based *ALDH2* genotype and health risk information [13]. In this previous study, the frequency and amount of drinking were significantly reduced after 30 days in the feedback group with low *ALDH2* activity. However, their follow-up period was 30 days, which is shorter than 6 months (maintenance period) [28], for behavioral habituation and maintenance. Therefore, the strength of the current study is the investigation of the intervention effect until 6 months (maintenance period) [28], which is the standard duration for behavioral habituation, and verification of its long-term efficacy.

Conversely, one limitation of this study is that when students agree to participate, they already know if they are in the group to be tested or not; hence, they cannot be blinded. Regarding the primary outcome measure, the average drinking amount on the drinking day is limited to the calculation of the amount of drink with an unknown alcohol concentration or amount. In addition, given that this research deals with genetic information, we need to evaluate the intervention effect by interviewing each participant. We also need to examine a system that can be useful for enrolling large groups, such as university students.

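### The drinking calendar, as described, cannot separate alcohol-free days from unrecorded days, and encouragement to keep it differs by arm; this matters if a calendar total is analysed

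*Protocol article*

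**What the plan says.** **What is recorded.** Under Primary outcome measures, "the drinking contents (alcohol type and alcohol concentration) and amount on the day of drinking will be recorded for half a year". The abstract's Methods agree: participants "recorded the drinking days and amounts on the drinking calendar". The article describes no entry for a day without alcohol.

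**How it is reduced.** "From the record of the calendar, the sum of the drinking amount (pure alcohol amount) and the number of drinks is calculated", using the usual volume-to-grams formula. No period, no count of completed days and no rule for blank days is given.

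**Which quantity is primary.** Primary outcome measures names the "average amount of daily drinking (g = pure alcohol, 1 drink = 10 g of pure alcohol"). The same section describes a questionnaire item: "We ask the answer of the average number of drinks on the drinking day of the past month". Statistical analysis compares "changes in the average daily drinking amount (1 drink = 10 g of pure alcohol) before and after intervention" between the groups, and also lists the amount on drinking days among the data to be described. The limitations in the Discussion begin: "Regarding the primary outcome measure, the average drinking amount on the drinking day is limited".

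**Who is encouraged to record.** Measures asks for the half-year calendar by e-mail, with an optional reminder after non-response, and does not distinguish the arms. Under Actual intervention, the session draws on the participant's calendar records and suggests continuing the diary and calendar as self-monitoring. For controls, Conventional teaching materials says: "The survey will only be conducted for half a year by providing the conventional materials". The handbook contents listed there include no advice to keep a calendar.

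**The concern.** A total built from drinking-day entries treats every blank day as 0 g, whatever the reason for the blank. If recording fades over six months, recorded consumption falls even when true consumption does not. A before-after change computed from the calendar would then look better than it is in both arms.

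The between-arm comparison is distorted when recording fades differently. There is a reason to expect that it might: the outcome instrument is also a component of the intervention, reviewed and encouraged in one arm of an open-label trial. If counselled participants record more fully, controls appear to drink less and a real benefit is masked. If counselled participants leave more drinking days blank, a benefit appears that is not there. The calendar as described could not show which had happened.

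Alcohol-free days also matter in their own right. The result report covers liver rest days, and the session materials mention that no daily drinking may be desirable. Days without alcohol are thus something the intervention may change, and they are the days the calendar leaves unmarked.

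**Working it through.** The documents give no figure for calendar completeness, so there is none to reproduce. The steps below show the mechanism. All recording rates and intakes are assumptions.

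**1. Formula.** If lapses are unrelated to the amount drunk, recorded total = true total × share of drinking days recorded. With equal true intake, the ratio of control to intervention totals is the ratio of those shares.

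| Recorded, intervention | Recorded, control | Control ÷ intervention | Spurious difference |
|---|---|---|---|
| 90% | 90% | 1.000 | none |
| 90% | 80% | 0.80/0.90 = 0.889 | control 11% lower |
| 95% | 70% | 0.70/0.95 = 0.737 | control 26% lower |
| 80% | 90% | 0.90/0.80 = 1.125 | intervention 11% lower (0.80/0.90) |

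**2. In grams.** Assume 40 g per drinking day and 10 drinking days in 30. The true mean is 40 × 10/30 = 13.33 g per calendar day.

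- No true effect, 20% of drinking days blank in controls and 10% in the intervention arm: 10.67 against 12.00 g/day. The intervention arm looks 12.5% higher.
- True reduction of 20%, same lapses: control 10.67, intervention 13.33 × 0.80 × 0.90 = 9.60. The apparent reduction is 10%.
- True reduction of 20%, lapses of 30% and 10%: control 9.33, intervention 9.60. The intervention arm looks 2.9% higher.

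**3. Why the calendar cannot resolve it.** A participant who truly cuts from 10 to 8 drinking days has 8 × 40/30 = 10.67 g/day. A participant who still drinks on 10 days but records 8 has the same entries and the same 10.67.

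**4. The per-drinking-day average.** In both cases it is 8 × 40/8 = 40 g. It is therefore unaffected by lapses unrelated to amount. It also stays at 40 g for the participant who really gave up two drinking days, so it misses that change.

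**5. What a denominator of marked days does.** Suppose 20% of all days go unmarked, regardless of drinking. Then 24 days are marked, 8 of them drinking days: 320 g. Dividing by 30 gives 10.67. Dividing by the 24 marked days gives 13.33, the true value. This works only if unmarked days resemble marked ones.

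**6. Scale.** If the SD of intake were 0.5 to 1.5 times the mean (assumption), an 11% distortion would be 0.11/0.5 = 0.22 down to 0.11/1.5 = 0.07 SD. Sample size states an effect of 0.2 without naming the metric. Its total of 199 reproduces as a two-group comparison with f = 0.2, that is d = 0.4 (198.16), or as a paired comparison with dz = 0.2 (198.15).

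**The case against.** The strongest reply is that the calendar total may not be the analysed outcome. The Discussion names the primary measure per drinking day, the questionnaire asks for it that way, and baseline intake is taken by questionnaire at consent and confirmed with the participant. None of these depends on calendar completeness. This stands, and it makes the point conditional. It does not remove it: the calendar and its sum are described under the primary outcome heading, the outcome is elsewhere called average daily drinking, and a per-drinking-day figure cannot supply a daily average.

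A reader might infer that the plan counts unfilled days as abstinence. No such rule is stated. The effect follows only from summing drinking-day entries over a period, and the sentence could also mean adding up the drinks within one day.

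A reader might also infer that only the intervention arm is asked to keep recording. That is not so. Both arms are asked for half a year with the same e-mails. The difference is the review and added encouragement in one session. The reminder is sent when there is no response, so it does not address blank days inside a returned calendar.

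Finally, an article may leave the calendar form to the full protocol. If that form already has a did-not-drink box, the recording part is closed by confirming it. The unsettled source and denominator remain, because they lie in the article's own wording.

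**Conclusion.** The point holds as a conditional risk and a cheap improvement. As described, the calendar total and any grams-per-calendar-day figure derived from it cannot distinguish abstinence from non-recording, and encouragement to record is not the same in the two arms. If that total is analysed, the contrast could be biased either way.

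The documents do not show that differential lapsing occurs, in which direction, or how large it is. The 11% figure rests on assumed recording of 90% against 80%. Equal lapsing gives no relative bias between arms, though it would still distort within-arm changes taken from the calendar if recording fades. It would be wrong to conclude that the primary outcome is biased: if the primary outcome is the questionnaire's average per drinking day, calendar lapses do not reach it. The cost of that choice is that added alcohol-free days go unmeasured. The article should say which it is.

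**What to change.** - In both arms, require a mark for every calendar day, including an explicit did-not-drink tick.
- Compute grams per day as total grams divided by marked days, zeros included, and treat unmarked days as missing.
- Report marked days by arm and by period, so that readers can judge whether completeness differs.
- Send identical calendar-completion prompts to both arms on the same schedule.
- State which source (questionnaire or calendar) and which denominator (drinking day or all marked days) define the primary outcome, and use the same term throughout Primary outcome measures, Statistical analysis and Discussion.
- For calendars already returned without zero marks, ask about blank days in the next survey e-mail.

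The cost is one extra tick per day and a changed denominator, with no new visits or staff. Some blanks in calendars already returned will stay uncertain. Dividing by marked days does not help if people skip marking mainly on days they drink, so completeness by arm needs to be shown beside the result.

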### Secondary outcome measures

As the secondary outcomes, screening test (AUDIT-C and AUDIT) scores, awareness of participant’s flushing reaction (simple flushing questionnaire method two items) [3], recognition of constitution strength against alcohol, and recognition of drinking amount by 5-step Likert scale are examined. AUDIT, which consists of ten self-written questions, was prepared by the World Health Organization as a screening method for excessive drinking. Hiro et al. verified the effectiveness and validity of the Japanese version of the questionnaire [25], and in the current guidance for AUDIT SBI in Japanese health guidance, an AUDIT score of 7 points or less is considered low-risk drinking, whereas an AUDIT score of 8 points or more suggests excessive drinking [26]. AUDIT-C is a simple screening test (maximum score of 12 points) composed of the first three items of AUDIT, and in Japan, 6 points or more for males and 4 points or more for females are considered excessive drinking, corresponding to 8 points or more of AUDIT [27].

Furthermore, we will investigate the five stages of change in drinking behavior: precontemplation, contemplation, preparation, action, and maintenance [28]. Self-recognition of the genetic constitution of alcohol-metabolizing enzymes will also be conducted. In addition, we will evaluate the modified Perceived Health Competence Scale (modified PHCS) Japanese version [29], the impact on learning by drinking over the past month, sleep condition, the Subjective Fatigue Scale for Young adults (SFS- Y) [30], and recognition of the usefulness of genotype test on alcohol-metabolizing enzymes in health care.

Japan’s Ministry of Health, Labor, and Welfare has listed support technology in the “Standard Health Checkup and Health Guidance Program Definitive Edition” and calls for “indifference, interest, preparatory period, execution period, and maintenance period” as “the preparation stage for behavior change,” and “to support the stage to improve by changing the support method for each stage” (definitive edition p86, revised version p121, 2018 edition p3-2) [31]. The five stages are as follows: (1) indifference period, lack of intention to take action toward behavior change within 6 months; (2) period of interest, willingness to take action toward behavior change within 6 months; (3) preparation period, willingness to take action toward behavior change within 1 month; (4) implementation period, observance of a clear behavior change at less than 6 months only; (5) maintenance period, clear behavior change lasting for more than 6 months [28]. In this study, the survey was conducted at baseline and four points up to half a year.

The modified PHCS Japanese version [29], which has eight items (5-step Lickert scale), was created by Smith, Wallston, and Smith (1995) according to self-efficacy theory as a performance index involved in changes in health-related habits and behavior. Its reliability and validity were verified by Togari et al. [29]. In addition, while alcohol has a hypnotic effect, drinkers are easily awakened because of the decrease in the blood concentration of alcohol and diuretic action after falling asleep; in fact, the association between binge drinking and sleep problems was suggested in young adults in particular [32]. Therefore, the presence or absence of binge drinking (within 2 h, >5 drinks for males and >4 drinks for females) and sleep status (recognition of sleep time and sleep quality: 4-step of Likert scale, difficulty falling asleep, and wakefulness during sleep) in the past month were added to our questionnaire. In addition, fatigue conditions will be investigated using SFS-Y [21], considering that the burden on the liver by excessive drinking leads to fatigue. We will also investigate the effect on class attendance and assignment submission on a 5-step Likert scale. SFS-Y has 24 items (6 subscales: difficulty in intensive thinking, fatigue, decreased motivation, decreased vitality, drowsiness, body discomfort), and it has been proven to be reliable and valid [21].

